# Decreasing Delirium through Music (DDM) in critically ill, mechanically ventilated patients in the intensive care unit: study protocol for a pilot randomized controlled trial

**DOI:** 10.1186/s13063-017-2324-6

**Published:** 2017-11-29

**Keywords:** Delirium, Music, Critical care

## Abstract

**Background:**

Delirium is a highly prevalent and morbid syndrome in intensive care units (ICUs). Changing the stressful environment within the ICU via music may be an effective and a scalable way to reduce the burden of delirium.

**Methods/design:**

The Decreasing Delirium through Music (DDM) study is a three-arm, single-blind, randomized controlled feasibility trial.

Sixty patients admitted to the ICU with respiratory failure requiring mechanical ventilation will be randomized to one of three arms (20 participants per arm): (1) personalized music, (2) non-personalized relaxing music, or (3) attention-control. Music preferences will be obtained from all enrolled participants or their family caregivers. Participants will receive two 1-h audio sessions a day through noise-cancelling headphones and mp3 players. Our primary aim is to determine the feasibility of the trial design (recruitment, adherence, participant retention, design and delivery of the music intervention). Our secondary aim is to estimate the potential effect size of patient-preferred music listening in reducing delirium, as measured by the Confusion Assessment Method for the ICU (CAM-ICU). Participants will receive twice daily assessments for level of sedation and presence of delirium. Enrolled participants will be followed in the hospital until death, discharge, or up to 28 days, and seen in the Critical Care Recovery Clinic at 90 days.

**Discussion:**

DDM is a feasibility trial to provide personalized and non-personalized music interventions for critically ill, mechanically ventilated patients. Our trial will also estimate the preliminary efficacy of music interventions on reducing delirium incidence and severity.

**Trial registration:**

ClinicalTrials.gov, Identifier: NCT03095443. Registered on 23 March 2017.

**Electronic supplementary material:**

The online version of this article (doi:10.1186/s13063-017-2324-6) contains supplementary material, which is available to authorized users.

## Background

Delirium is characterized by a disturbance of consciousness, the presence of inattention, disorganized thinking, and a fluctuating course [1]. It has an incidence as high as 85% in mechanically ventilated patients, and is associated with longer hospital stays, increased hospital and post-discharge mortality as well as higher healthcare costs [2–6]. Furthermore, over 30% of patients with delirium experience long-term cognitive impairment [7].

Despite the incidence and morbidity associated with delirium, effective pharmacological and non-pharmacological interventions to treat this condition are lacking. Music listening is a unique, non-pharmacological intervention that may reduce delirium incidence and severity through the inhibition of inflammation. Prior music listening research has demonstrated a calming effect with slow-tempo music. This is hypothesized to be secondary to entrainment of the autonomic nervous system, reduction in sympathetic activation and dampening of the inflammatory state [8]. With various pathophysiological models for delirium implicating neuro-inflammation, neurotransmitter imbalances and an aberrant stress reaction, [9] this makes music listening a promising intervention to prevent or treat delirium.

Music intervention studies in the intensive care unit (ICU) have focused on its effects on anxiety, pain, tolerance of non-invasive ventilation, and physiological indicators of the stress response (heart rate, blood pressure, catecholamines, cortisol), but, to date, studies on the effect of music listening on ICU-related delirium have not been conducted [10–16]. Our study aims to test the feasibility of music listening, and estimate the potential effect size of music listening on delirium, in critically ill patients on mechanical ventilation.

## Methods/design

### Rationale

We are conducting a feasibility trial to deliver personalized music for critically ill patients based on preferences supplied by their surrogates or family members. Participants in the study are unlikely to be able to communicate or choose their own music due to invasive mechanical ventilation, the need for high ventilator support, and hemodynamic instability. Our study design also includes single blinding and three intervention arms (personalized music, non-personalized, investigator-selected music, and attention-control) which adds complexity to the unique ICU environment.

Our study aims to gather data to help inform a definitive randomized controlled trial.

### Outcomes

Our study aims to answer the following question: In critically ill patients on mechanical ventilation, is the design and implementation of music listening feasible?

The primary outcomes of our study are: (1) to assess recruitment rates, described by the number of participants approached and their rates of consent, (2) to assess adherence to the intervention by number of listening sessions completed per patient, and (3) to assess retention by the number of participants completing the study.

The secondary outcome in the study is to estimate the potential effect size of patient-preferred music in reducing delirium incidence as measured by the Confusion Assessment Method for the ICU (CAM-ICU).

### Design

DDM is a feasibility study with a three-arm, single-blind, randomized controlled design.

Patients admitted to the ICU with respiratory failure requiring mechanical ventilation are eligible. Sixty participants will be randomized to one of three arms (20 patients per arm): (1) personalized music, (2) non-personalized relaxing music, or (3) attention-control (see Fig. 1). Participants will receive two 1-h audio sessions a day through noise-cancelling headphones (and mp3 players). We chose an attention-control arm (rather than usual care) to test the feasibility of a placebo, and to control for the non-specific effects of headphone and non-audio sounds in the study.

**Fig. 1 Fig1:**
[figure not shown]
DDM study flowchart, interventions, and assessments. Abbreviations: *CAM-ICU* Confusion Assessment Method for the Intensive Care Unit, *CPOT* Critical Pain Observation Tool, *Katz* Katz Index of Independence in Activities of Daily Living, *Lawton* Lawton Instrumental Activities of Daily Living, *RASS* Richmond Agitation-Sedation Scale, *VASA* Visual Analog Scale for Anxiety

The trial protocol was written according to the Standard Protocol Items: Recommendations for Interventional Trials Statement (SPIRIT). A SPIRIT Figure is provided (see Fig. 2) and a SPIRIT Checklist is included as Additional file 1.

**Fig. 2 Fig2:**
[figure not shown]
Standard Protocol Items: Recommendations for Interventional Trials (SPIRIT) Figure for the DDM Trial. Abbreviations: *CAM-ICU* Confusion Assessment Method for the Intensive Care Unit, *CPOT* Critical Pain Observation Tool, *ICU* intensive care unit, *IQCODE* Informant Questionnaire on Cognitive Decline in the Elderly, *RASS* Richmond Agitation-Sedation Scale

### Setting

Patients admitted to the medical or surgical ICU service at Sidney and Lois Eskenazi Hospital (Indianapolis, Indiana) are eligible. Eskenazi Hospital is a busy 618-bed, urban, safety net hospital with 44 ICU beds (22 surgical, 22 medical), averaging 120 ICU admissions per month. Demographics of this ICU are: mean age of patients 53.7 years, 45% African American, 47% female, 29% age 60 years or older, and 16% with Medicaid insurance.

### Participants

The target population for our trial is adults aged 18 years and older, admitted to the medical or surgical ICU on invasive mechanical ventilation.

### Consent

Individuals deemed eligible for the study will be approached for consent. If on mechanical ventilation and unable to consent, the patient’s surrogate or healthcare representative will be approached for consent.

### Inclusion criteria

Inclusion criteria for our study are: (1) age 18 years or older, (2) English speaking, (3) admitted to the ICU (medical or surgical), and (4) receiving mechanical ventilation for an anticipated duration of 24 h or longer, provided that the patient has not already been on the ventilator longer than 48 h at the time of enrollment.

### Exclusion criteria

Patients are excluded from our study if any of the following conditions are present: (1) severe dementia or chronic neurological disease, with an IQCODE score of 4.5 or greater; [17–19] (2) acute or subacute severe neurological deficit or injury; (3) severe psychiatric illness (not including depression) or developmental problems; (4) suspected or confirmed drug or alcohol intoxication/overdose or withdrawal; (4) uncorrected or severe hearing or vision impairment; (5) coma after cardiac arrest and/or hypothermia protocol; (6) pregnant or nursing women; (7) prisoners; (8) expected death within 24 h of enrollment or lack of commitment to aggressive treatment by family or the medical team; (9) inability to obtain consent from legally authorized representative within 72 h of meeting eligibility; and (10) attending physician or healthcare team refusal.

### Materials

Participants are provided with noise-cancelling headphones (Maxell NC-IV Superior Noise Cancellation), with mp3 player devices (Apple iPod Shuffle 2GB, 6th generation or Goldenseller 16GB Mp3 Player) during the trial. Music tracks and audiobooks were purchased from Apple Music Store (iTunes).

## Study procedures

### Screening

Patients admitted to the ICU are screened on a daily basis. Music preference data will be collected from all enrolled participants (through their surrogates) regardless of intervention arm.

### Participant randomization

Using a computer-generated list of random numbers created by study statistician, participants are randomized by permuted block with varying block sizes. Randomization occurs within 48 h of enrollment in a 1:1:1 ratio, and only the unblinded study coordinator, who also programs the music devices, is aware of the randomization assignment.

### Study duration/termination

The music intervention period is 7 days post randomization. Participants will stop receiving music sessions early if they choose to withdraw, are transferred out of the ICU, die, or are discharged. In-hospital follow-up continues to 28 days or until discharge, whichever occurs earlier, by daily assessment, unless they choose to withdraw. All participants will be invited for follow-up in the Critical Care Recovery Clinic at 90 days.

### Pre-intervention phase

Upon enrollment, demographics, clinical data (vital signs, pertinent laboratory and imaging data), severity of illness (APACHE II and SOFA), comorbidity burden (Charlson Comorbidity Index), pertinent home medications, reason for admission, pre-hospital functional status (Katz and Lawton), and cognitive function (Informant Questionnaire on Cognitive Decline in the Elderly (IQCODE)) are obtained [20–23]. Cumulative doses of antipsychotic, analgesic, sedative, and anxiolytic medications are also recorded.

A previously described music-preference assessment tool is utilized to obtain the participants’ music preferences from family members/surrogates [24]. We collect information about genre likes and dislikes, as well as specific favorite artists, tracks, and instruments.

A pre-intervention level of consciousness and delirium assessment is performed upon enrollment through the Richmond Agitation Sedation Scale and the CAM-ICU, respectively [3, 25].

### Playlist development

Following enrollment consent, blinded research personnel enter the participant’s music preferences into a Research Electronic Data Capture (REDCap) database. The unblinded study coordinator programs music devices based on an individual study participant’s randomization status. For those randomized to personalized music, Apple Music is utilized to create a playlist based on their musical interests.

Participants randomized to non-personalized music received an mp3 player programmed with slow-tempo, relaxing music and instrumental sounds (piano, relaxing rainfall sounds, and classical music). Finally, participants randomized to attention-control receive a device with audiobooks. The audiobooks include *Treasure Island*, *Harry Potter*, and [name] *Oh the Places You’ll Go!*, and were chosen for their readability and for their broad appeal.

The playlist for each participant is carefully tracked, which will permit subsequent analysis should particular books or tracks be associated with increased delirium incidence or severity.

To avoid unblinding study personnel to the intervention arm, the coordinator waits a minimum of 4 h to release the mp3 device for use in the study. Prior to allocating devices to patient rooms, all devices are checked to ensure that identifying data including name, artist, collection, and genre have been removed, the device is clean and in good functioning order, and volume is set to a pre-specified level.

### Intervention phase

Music listening sessions are twice a day, for 1 h at a time, from 10:00 to 11:00 and 14:00 to 15:00, for 7 days. The times are based on feedback from ICU nurses associated with least interference with clinical activities. Music listening is provided for 7 days unless the participant refuses, withdraws, is transferred out of the ICU, or dies. Participants extubated within the 7-day period continue to receive the intervention unless they are transferred out of the ICU. Participants remaining in the ICU after 7 days will not receive further intervention due to the resource limitations of our feasibility study.

During listening sessions, a conducive listening environment is created; medical teams are asked to avoid non-urgent patient care activities, the in-room television is turned off, family members are asked to limit their interactions with the patient, and the door is closed to limit outside noise. As all three arms of the trial will receive a conducive listening environment, and due to the use of noise-cancelling headphones in these settings, we believe that the audio dose will remain as the pure active intervention.

Participants receive their first dose of music listening, in one of these windows, as soon after enrollment as possible.

The ICU clinical nurses receive on-site training in the study protocol, and in the operation of the music devices and headphones. Blinded research personnel and/or hospital nurses start the music sessions by placing the headphones on the participants and activating the audio. Adherence is monitored by recording the start and stop date and times for each session. The participant’s heart rate and blood pressure pre and post session are also recorded.

All participants in the trial receive the ABCDEF bundle that is standard of care in the ICU where the study is being conducted. The ABCDEF bundled delirium care protocol places a multidisciplinary focus on daily ventilator liberation trials, sedation vacation, choice and optimization of sedation, nursing-led delirium screenings, early mobility, and family/social support [26]. Participants in the study will continue to have physician-determined sedation without input on choice of sedation from our trial.

### Blinding during intervention

We are using various measures to ensure concealment of a participant’s allocation. Only the unblinded study coordinator programs the audio devices, and ensures that the tracks are anonymized (renamed to a series of digits or letters), to prevent unblinding when bedside staff view the audio device’s screen. Our protocol also benefits from the fact that the majority of audio devices lack screens entirely (Apple iPod Shuffle). Participants, their family members/surrogates, and hospital nurses are asked not to share a patient’s randomization with anyone in the study, should they become aware of it. Audio is not turned on until the headphones are securely placed on the participant to prevent study personnel from inadvertently hearing the output. Participants are permitted to change tracks or adjust the volume if needed. Should one of the study personnel become unblinded, they are reassigned to other study participants. To assess the fidelity of these efforts, we will survey research personnel to predict patient randomization in a subset of participants.

### Assessments during intervention

All assessments are performed by blinded research assistants. Assessments occur twice a day, approximately at 11:00 and 15:00 (after audio interventions). Study personnel perform the following: (1) Richmond Agitation-Sedation Scale (RASS) to document level of consciousness; (2) Confusion Assessment Method for the ICU (CAM-ICU) to screen for delirium [3, 25, 27], and CAM-ICU-7 to determine delirium severity [28]; (3) Critical Care Pain Observation Tool (CPOT) to determine level of analgesia and symptom control [29]; (4) Faces Anxiety Scale (performed after the morning listening session) [30, 31]; (5) physical therapy and occupational therapy notes are evaluated and each participant’s mobility milestones are recorded using Hodgson Mobility Scale [32]; and (6) adverse events are assessed (including seizures while listening, localized skin breakdown or cellulitis around the ears) and are reported to the Institutional Review Board (IRB) per usual protocol.

### Post intervention

Participants receive in-hospital assessments by blinded research personnel until hospital discharge, day 28, or they withdraw or die. Twice a day, at approximately 11:00 and 15:00, study personnel perform the RASS, CAM-ICU, CAM-ICU-7, CPOT, and the Faces Anxiety Scale, evaluate mobility with the Hogdson Mobility Scale, and record adverse events.

Beginning within 72 h of extubation or removal of the endotracheal tube, and if the patient is CAM-ICU negative, the participant is reconsented for the study. The participant is also screened for obstructive sleep apnea with STOP-BANG and the Richards-Campbell Sleep Questionnaires, given the higher incidence of delirium in patients with sleep apnea and disturbed sleep quality [33–35].

### Follow-up

Participants are invited to follow-up in the Critical Care Recovery Center (CCRC) at 90 days from hospital discharge. The CCRC is an outpatient interdisciplinary clinic comprising care coordinators (social worker, nurse), a critical care physician, psychometrician, and psychologist. Its goal is to maximize the cognitive, physical, and psychological recovery of ICU survivors through comprehensive assessments and personalized recovery plans incorporating self-management protocols.

### Data collection

Prior to the trial initiation, study personnel underwent training sessions on data collection and were individually tested on data entry as well as outcome assessments.

Study data have been collected and managed using REDCap electronic data capture tools hosted at Indiana University. REDCap is a secure, web-based application designed to support data capture for research studies, providing: (1) an intuitive interface for validated data entry; (2) audit trails for tracking data manipulation and export procedures; (3) automated export procedures for seamless data downloads to common statistical packages; and (4) procedures for importing data from external sources.

On a daily basis during all phases of the study and for up to 28 days, blinded personnel collect vital signs, pertinent laboratory and imaging data, data to calculate severity of illness, clinical events including surgery and tracheostomy, duration and modes of mechanical ventilation, cumulative daily doses of sedatives, analgesics, antipsychotics, presence of shock requiring vasopressors, and the administration of systemic steroids or paralytic agents. We also collect disposition at discharge.

### Sample size and feasibility

We determined criteria for feasible recruitment rates based on prior research. A large trial of music in the ICU had a recruitment rate of 33%, while delirium studies have had recruitment rates close to 30% [11]. Our own recruitment experience at the institution where this trial is being conducted suggests recruitment rates near 60%. Given a sample size of 60 participants, we will be able estimate a recruitment rate of 60% to within a 95% confidence interval of ± 12.40%. A recruitment rate of 48% would be lower than our institutional norm, but remains higher than other similar trials.

Adherence to the intervention will be defined as the percentage of audio sessions completed per patient (a maximum of 14 sessions per patient at a rate of two sessions per day for 7 days), adjusted for number of eligible sessions based on length of stay in the ICU. Our sample size of 60 participants will permit an estimate of the adherence rate of 80% to within a 95% confidence interval of ± 10.12%. We determined a retention rate of 80% for feasibility, defined by the percentage of participants completing all in-hospital components of the study, which can be estimated with a similar confidence interval. As a pilot study, we anticipate that a sample size of 60 participants will be sufficient to determine feasibility.

Our pilot study will help calculate sample size needed for a definitive randomized controlled trial. A decrease of 15% in delirium incidence between groups would make a larger trial feasible, with a three-arm trial requiring 548 participants (allowing 20% for attrition, *α* = 0.05, power = 80%).

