### Trial status

Enrollment is ongoing. Recruitment began in December 2016 and is expected to conclude in January 2018. Target enrollment for the study is 60 participants. The trial was retroactively registered at ClinicalTrials.gov.

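### The ±12.40% precision for the recruitment rate is computed on the 60 enrolled participants, not on the roughly 100 who would have to be approached; the true half-width is about ±9.6 points

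*Protocol article*

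**What the plan says.** The Outcomes section of the protocol article lists recruitment as the first primary outcome: "to assess recruitment rates, described by the number of participants approached and their rates of consent". The Design section fixes the trial size: "Sixty participants will be randomized to one of three arms (20 patients per arm"). Trial status repeats it as an enrollment figure: "Target enrollment for the study is 60 participants".

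Under Sample size and feasibility, the anticipated rate comes from local experience: "Our own recruitment experience at the institution where this trial is being conducted suggests recruitment rates near 60"%. The precision claim follows: "Given a sample size of 60 participants, we will be able estimate a recruitment rate of 60% to within a 95% confidence interval" of ±12.40%. The next sentence reads: "A recruitment rate of 48% would be lower than our institutional norm, but remains higher than other similar trials". The similar trials are those cited just before it, with rates of 33% and close to 30%. The same section uses 60 participants for adherence at 80%, with a half-width of ±10.12%, and says that retention at 80% can be estimated with similar precision. The article gives no number of patients to be approached.

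**The concern.** A consent rate among patients approached has the number approached as its denominator. The 60 participants are those who agreed and were randomized, so they are the numerator. A half-width computed with 60 underneath describes a study that approaches 60 patients and, at the assumed rate, enrolls about 36. That is not this trial.

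Recruitment is the first primary outcome of a feasibility trial, and the sample size is justified by how precisely the feasibility rates can be estimated. A misstated half-width there is a misstated property of the design. The 48% in the following sentence may also have been read off the same interval.

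**Working it through.** **Inputs.** Anticipated recruitment rate p = 0.60, n = 60 and stated half-width ±12.40 points (Sample size and feasibility). Rate defined on patients approached (Outcomes). Sixty randomized or enrolled (Design; Trial status). Adherence 80% ± 10.12 points with n = 60 (Sample size and feasibility).

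**1. Reproduce the stated figure.** Normal-approximation half-width = 1.96 × √(p(1 − p)/n).

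- p = 0.60, n = 60: 1.96 × √(0.24/60) = 0.1240, or ±12.40 points (47.6% to 72.4%). This matches.
- p = 0.80, n = 60: 1.96 × √(0.16/60) = 0.1012, or ±10.12 points. This matches the adherence figure.

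Other intervals for 36 of 60 do not give ±12.40: Wilson runs from 47.4% to 71.4%, Clopper-Pearson from 46.5% to 72.4%, and a t multiplier on 59 degrees of freedom gives ±12.66.

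**2. Could the 60 mean patients approached?** No. Adherence and retention exist only for enrolled patients. If 60 were approached at a 60% rate, 0.60 × 60 = 36 would enroll, and the half-width at 80% would be 1.96 × √(0.16/36) = 0.131, or ±13.1 points, not ±10.12. At the assumed rate, the two stated half-widths cannot both describe one trial. Since 60 enrolled is fixed elsewhere, the recruitment figure is the one that is off.

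**3. Use the right denominator.** Number approached = 60/0.60 = 100.

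- 1.96 × √(0.24/100) = 0.0960, or ±9.60 points (50.4% to 69.6%).
- Treating 60 consents as a fixed stopping count (inverse sampling) gives 1.96 × 0.60 × √(0.40/60) = 0.0960, the same.
- For 60 of 100, Wilson gives 50.2% to 69.1% and Clopper-Pearson 49.7% to 69.7%, so the choice of interval hardly matters.

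Ratio of stated to corrected half-width: 12.40/9.60 = 1.29, or about 29% too wide.

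**4. Other rates, with 60 consents.**

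| Consent rate | Approached | 95% half-width (points) |
|---|---|---|
| 60% | 100 | ±9.60 |
| 48% | 125 | ±8.76 |
| 33% | 182 | ±6.83 |
| 30% | 200 | ±6.35 |

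With the number approached equal to 60/p, the half-width is 1.96 × √(p²(1 − p)/60). This is largest at p = 2/3, where p²(1 − p) = 4/27, and equals 1.96 × √(0.1481/60) = 0.0974, or ±9.74 points. So ±12.40 is not reached at any consent rate.

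**5. The 48%.** 60 − 12.40 = 47.60, which rounds to 48. The corrected lower limit is 60 − 9.60 = 50.40, or about 50.

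**The case against.** The strongest reply is that the slip changes no decision. Precision is better than promised, so the conclusion that 60 participants suffice is strengthened, and randomization, data collection and the planned tests are untouched. This stands, and it makes the point minor. It does not make the stated half-width right.

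A reader might infer that the 48% benchmark is therefore wrong. The article does not support that. It never calls 48% a confidence limit. It says only that this rate "would be lower than our institutional norm, but remains higher than other similar trials", which is true against about 60% locally and 30% to 33% elsewhere whatever the interval. No go/no-go rule is tied to 48%, and a feasibility floor need not equal a confidence limit. What remains is that 48% sits directly after the interval, equals its rounded lower limit, and has no other stated origin.

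A reader might also infer that the final recruitment interval will be computed on 60. Nothing in the article plans this; the outcome definition already points to the number approached.

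Last, the replacement figure is itself approximate. The rate counts consents, while the 60 are randomized, and Participant randomization allows up to 48 h between enrollment and randomization. If some who consent are never randomized, more than 100 must be approached and the interval narrows a little further. This qualifies ±9.6 but does not rescue n = 60.

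**Conclusion.** The point holds in a narrow form. The ±12.40% half-width uses the number enrolled as the denominator of a rate that the article defines on the number approached. On that definition the half-width is about ±9.6 points (50.4% to 69.6%).

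This rests on the article's own 60% rate, on the normal-approximation interval that reproduces its figures, and on every consenting patient being randomized. The error is confined to recruitment: for retention, 60 is the right denominator. It is in the safe direction and calls for no change in sample size. The link between 48% and the misstated interval is plausible but inferred. Severity: minor.

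**What to change.** Replace the precision sentence with: *To enroll 60 at a 60% consent rate, about 100 patients will be approached, giving a 95% confidence interval of about ±9.6 percentage points (50.4% to 69.6%).* Add that this assumes all who consent are randomized.

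For the 48%, add a clause on its origin. If it is a chosen threshold, say so and leave it. If it was meant as the lower confidence limit, update it to about 50%.

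The cost is a sentence or two of text. No additional patients, data or analyses are needed.
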